### Sample Size

2.6

Based on current methodologies, we performed an a priori sample size calculation using power analysis (Döring and Bortz 2016) with the G*Power 3 software (Faul et al. 2007). For this calculation, we assumed moderate effect sizes between dependent and independent variables (Cohen 1988), an alpha level of 0.05, and a power of 0.80. To test correlations between dependent variables (task load, time, guideline adherence) and four independent variables (use of the demonstrator, general load of the shift, professional experience, severity of wound) using multivariate models (multiple linear regression) under these assumptions, we will require a total of 85 nurses.

With a calculated sample size of 85 nurses and considering up to four independent variables, we anticipate obtaining meaningful results within a manageable timeframe and with the available resources. Accounting for a projected 10% dropout and missing rate, based on experiences from previous studies, we plan to recruit 95 nurses to ensure a sufficiently large sample for subsequent evaluation.

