The selected criteria include performing a finger pressure test or the transparent disk method in the presence of redness (recommendation 9.1), accurately assessing wound type and classification (recommendation 9.2), applying wound edge protection in cases of macerated wound edges or surrounding skin (recommendation 3.1), and ensuring pressure relief for pressure injuries (recommendations 5.1 and 5.5). The response options for these criteria are binary: ‘No’ or ‘Yes or not required’. Sum scores are calculated from the responses, assigning a score of 1 to ‘Yes or not required’ and a score of 0 to ‘No’. Interrater reliability is also measured in the study. Additionally, the nurse's task load during wound assessment, dressing change, and documentation is evaluated using the standardized and validated NASA TLX questionnaire (Human Performance Research Group n.d.).

Other covariates measured include the nurse's professional experience, wound severity, and the general workload of the shift, which is assessed on a 5‐point scale relative to the average.

To assess the accuracy of the AI predictions of wound type and wound classification in the clinical setting, the wound is independently assessed on‐site by a member of the study team, separate from the nurse's assessment and the AI prediction. This assessment serves as the ground truth for calculating the accuracy of the AI predictions regarding wound type and classification.

Additionally, the usability of the documentation systems used, namely the standard clinical documentation systems and the AI‐based digital system, will be assessed in both the control and intervention groups. Usability will be evaluated using the two‐item UMUX Lite questionnaire with a 7‐point Likert scale (Lewis et al. 2013) because of its brevity (Borsci et al. 2020) and comparability with other studies and the SUS scale (Lewis et al. 2013).

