### Analysis Plan

2.12

Once data collection is complete, we will use multiple linear regression models to examine the effects of the AI‐based digital system on the duration of wound assessment, dressing change, documentation, perceived task load, and guideline adherence. We will calculate an individual linear regression model for each dependent variable and incorporate potential covariates such as the nurses’ professional experience, wound severity, and the general load of the shift. Nominal and ordinal variables (use of the AI demonstrator, severity of the wound, general burden of the shift, and guideline adherence) will be dummy coded. We will then assess each model for linearity, homoscedasticity, and the absence of multicollinearity to satisfy the assumptions of linear regression. If these conditions are met, we will proceed with standard multiple linear regression, incorporating all independent variables as predictors. The f‐test will be used to examine the extent to which the independent variables predict the dependent variable, with R² indicating how much of the variance in the dependent variable can be explained by the independent variables. The t‐test will assess the significance of the predictors. To determine the specific contribution of the use of the demonstrator, we will calculate the explanatory power for both the full regression model and a reduced model without the demonstrator use variable, using the difference in explanatory performance to isolate the effect attributable to the demonstrator use. Datasets with missing socio‐demographic data for nurses, used only to describe the sample and not part of the statistical analysis, will still be included in the analysis. However, datasets with missing values for independent variables will be excluded entirely, and datasets with missing values for dependent variables will be excluded only from the specific model where the data is missing. The significance level is set at 0.05. As this is an exploratory study and a separate model is calculated for each dependent variable, no correction for alpha error is required. To analyze the interrater reliability of the observers, we will use Kendall's rank correlation coefficient (Kendall's tau). To determine the performance of the AI‐based application in the clinical setting, we will calculate its accuracy in predicting wound type and wound classification, using the on‐site assessment of a study team member as ground truth. Additionally, we will descriptively evaluate the usability of both the standard clinical documentation systems and the AI‐based application in terms of central tendency, variability, and distribution.

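### The 80% power at 85 nurses matches an overall regression F-test with four predictors, but the planned dummy coding gives at least seven, and no power is stated for the demonstrator coefficient

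*Protocol article*

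**What the plan says.** Section 2.6 (Sample Size) of the protocol article describes a G*Power calculation for multiple linear regression with "four independent variables (use of the demonstrator, general load of the shift, professional experience, severity of wound". On effect size it says only that "we assumed moderate effect sizes between dependent and independent variables". The error rates are "an alpha level of 0.05, and a power of 0.80". The result is that "we will require a total of 85 nurses", raised to 95 for a 10% loss. The section repeats that 85 is adequate for up to four independent variables.

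Section 2.10 (Measures) says of the general workload of the shift: "which is assessed on a 5‐point scale relative to the average". It gives no number of levels for wound severity.

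Section 2.12 (Analysis Plan) fits a separate model for each outcome and enters all independent variables. Among the nominal and ordinal variables it lists demonstrator use, "severity of the wound, general burden of the shift, and guideline adherence) will be dummy coded". An F-test covers the model as a whole and a t-test covers each predictor. Full and reduced models are also compared, "using the difference in explanatory performance to isolate the effect attributable to the demonstrator use".

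**The concern.** Sections 2.6 and 2.12 count the predictors differently. An ordinal variable with k levels is one variable on paper but k − 1 terms once dummy-coded. A power figure for four terms does not carry over to a model with seven or more, because the overall F-test spends its numerator degrees of freedom on every term.

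There is also a question of target. The hypothesis in section 2.1 (Objectives) concerns the application: less time, lower task load, better adherence. The overall F-test asks whether all predictors together explain variance, and it can be significant through the covariates alone. A reader who meets one power figure of 80% will naturally take it as the chance of detecting the effect of the application. The article does not state that quantity.

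**Working it through.** **Inputs from the article.** Alpha 0.05, power 0.80, four independent variables, 85 nurses, 10% loss and 95 to recruit (section 2.6). Shift load on five points (section 2.10). Dummy coding of shift load and severity, with all independent variables entered (section 2.12).

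**Assumptions.** Moderate effect: f² = 0.15, the conventional medium value for multiple regression. Wound severity: at least two levels (number not stated). Experience: one continuous term (form not stated).

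**Formula.** For a test of u terms in a model with p predictors, λ = f²·N, df1 = u, df2 = N − p − 1. Power is the probability that a noncentral F with these values exceeds the 5% critical value of the central F.

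**Step 1: reproduce the stated figure.** Overall test, u = p = 4, N = 85:
- λ = 0.15 × 85 = 12.75, df2 = 80, critical F = 2.486, power = 0.803.
- At N = 84 the power is 0.797, so 85 is exactly the smallest N that reaches 80%.
- 85 / 0.9 = 94.4, rounded up to 95. The recruitment target also reproduces.

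Other readings:
- One coefficient at f² = 0.15 (u = 1, p = 4) would need 55 nurses, so it is not the source.
- A single bivariate correlation of r = 0.3 gives ((1.960 + 0.842) / atanh 0.3)² + 3 = 84.9, which also rounds up to 85. That calculation makes no use of the four predictors named in the text, so the overall F-test is the likelier source.

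**Step 2: count the planned terms.** Demonstrator use 1, shift load 5 − 1 = 4, experience 1, severity k − 1. The total is 5 + k: 7 if severity is binary, 9 if it has four levels.

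**Step 3: overall F-test with the real count**, f² held at 0.15:

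| Predictors | df2 at N = 85 | Critical F | Power at N = 85 | N for 80% |
|---|---|---|---|---|
| 4 | 80 | 2.486 | 80.3% | 85 |
| 7 | 77 | 2.131 | 69.5% | 103 |
| 8 | 76 | 2.063 | 66.4% | 109 |
| 9 | 75 | 2.007 | 63.5% | 114 |
| 11 | 73 | 1.922 | 58.3% | 123 |

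If all 95 recruited nurses have complete data, seven predictors give 75.8% (λ = 0.15 × 95 = 14.25).

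**Step 4: the demonstrator coefficient**, u = 1, N = 85:
- Partial f² = 0.15: power 94.2% with 4 predictors and 94.1% with 7 or 9. The coding hardly matters.
- 80% power is reached at partial f² of about 0.095. With two equal groups f² = d²/4, so d = 2 × √0.095 ≈ 0.62 residual standard deviations.
- At d = 0.5, f² = 0.0625 and power is 62%.

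**The case against.** Several points on the other side have force.

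- **The powered test is not named.** The overall F-test is inferred, and the r = 0.3 calculation gives 85 as well. This stands, so the match should be presented as the likelier reading and not as fact. It does not rescue the figure, since a bivariate calculation would not be power for the planned regression either.
- **The F-test is not said to confirm the hypothesis.** Section 2.12 gives that job to the t-tests of individual predictors. This stands. A reader might infer that the plan can show only a change in R², which has no sign or unit. The documents do not support that: the t-test concerns a signed coefficient in the outcome's own units, and for a single term the test of the R² difference is equivalent to it.
- **The hypothesis test is not harmed by the coding.** This also stands. A reader might infer that the test of the application is underpowered. The documents do not show that: its power is about 94% if its partial f² is 0.15, and the 62% figure needs a smaller effect and an equal split that the article does not state.
- **Holding f² at 0.15 is a choice.** Dummy coding cannot lower the population R² and may raise it. With seven predictors, 80% power at N = 85 returns at f² = 0.185, that is R² = 0.185 / 1.185 = 15.6% against 0.15 / 1.15 = 13.0%. This is a fair condition on the size of the loss. But section 2.6 claims no such larger effect.
- **It is an exploratory pilot with recruitment well advanced.** True, and it lowers the severity. But the article publishes an a priori power claim, and section 2.11 says control recruitment ran until the required sample size was reached.

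**Conclusion.** The point holds in limited form. Sections 2.6 and 2.12 disagree on the number of model terms, and the 80% is not delivered for the test that it most plausibly describes. Overall power at 85 nurses is 69.5% with seven predictors and 63.5% with nine. This rests on f² = 0.15 for the whole model, experience as one continuous term, and two or four severity levels respectively. Seven is the minimum count under that form of experience.

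Separately, no power is stated for the demonstrator coefficient, so the 80% should not be read as power for the effect of the application. That coefficient's power depends on a partial effect the article does not fix, and hardly at all on the coding, leaving aside any correlation between demonstrator use and the covariates. The arithmetic behind 85 and 95 is itself sound. This should be fixed, but it does not undermine the trial.

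**What to change.** In section 2.6, name the test and the numeric effect size behind the 85. Then add the power for the 1-df test of demonstrator use: 85 evaluable nurses give 80% power at partial f² of about 0.095, a standardised difference of about 0.62 assuming an equal split. Label this as what the sample can detect, not as the original basis for its size.

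If the overall F-test figure is kept, restate it for the actual number of dummy terms once the severity levels and the form of experience are given.

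In section 2.12, name the already planned demonstrator coefficient, with its 95% CI, as the main reported effect for each outcome, and keep the R² difference as a supplement.

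Entering shift load and severity as single ordinal scores would restore four predictors, but it imposes linearity. It is an optional modelling choice and is not required.

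The cost is wording in two sections. No extra nurses are needed. The stated overall power becomes less favourable. Intervention data collection was still ongoing when the article was written, so by that timetable the change could be made before analysis.

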### Recruitment

2.7

A dedicated electronic wound reporting system will be utilized to identify wounds that meet the inclusion and exclusion criteria. Due to the absence of an electronic reporting system for IAD and the likelihood that many wounds are not electronically documented, the research team will contact the included wards daily by telephone. They will inquire about new cases of PI or IAD or the admission of patients with existing PI or IAD wounds. Each patient is only included once in the study.

If wounds that meet the inclusion and exclusion criteria are identified, the study team will arrange for the next scheduled wound care appointment. At this appointment, the study team will inform the patient's nurse about the study. If the nurse in charge declines participation, no observation or survey will be conducted at that time. Still, the patient may be re‐enrolled at the next wound care appointment if the subsequent nurse agrees to participate. If the nurse consents in writing to participate, the study team will proceed with the observation of wound care and documentation. After completing the wound documentation, the nurse will complete an online questionnaire on a tablet, which includes questions about demographic data, general workload of the shift, task load, and the usability of the documentation system used. The study primarily targets new wounds and newly admitted patients with wounds. Due to organizational factors, there may be delays in some cases, including weekend admissions, nurses refusing to participate, and delayed documentation of new wounds.

To encourage participation, we engaged local wound experts and ward managers in the development of the digital system in the KIADEKU qualitative sub‐study and as key users during its implementation on the wards to enhance user acceptance. Additionally, nurses who agree to participate will receive vouchers as compensation for the extra effort involved in the study. These measures are anticipated to help achieve the sample size determined by the a priori sample calculation.

After careful consideration, obtaining patient consent was deemed unnecessary. This decision was based on the fact that wound management in the study aligns with standard practice, with the only variation being the documentation tool used. Furthermore, the study does not collect data that could identify patients. Nonetheless, the study team informs patients about the study before administering wound care.

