The visual similarities between IAD and PI, particularly in their early stages and common gluteal location, frequently lead to uncertainty and misclassification in nursing practice (Beeckman et al. 2008; LeBlanc et al. 2016). Despite the availability of validated assessment tools like the European Pressure Ulcer Advisory Panel (EPUAP) guidelines (European Pressure Ulcer Advisory Panel, National Pressure Injury Advisory Panel, & Pan Pacific Pressure Injury Alliance (2019)) and the Ghent Global IAD Categorization Tool (GLOBIAD), differentiating between these wound types remains a challenge for nurses (Beeckman et al. 2017, 2018; Francis 2019). Furthermore, studies suggest that nurses often possess limited knowledge about IAD (Barakat‐Johnson et al. 2022; Zhang et al. 2021), and misconceptions in assessing these wounds can lead to inappropriate intervention choices and delays (Beeckman et al. 2010). Beyond these assessment difficulties, challenges in wound documentation also persist. Research indicates that wound documentation frequently fails to capture all details of the assessment and care (Do et al. 2021; Gillespie et al. 2014; Li and Korniewicz 2013; Topaz et al. 2016). Issues such as irregular wound shapes, localization, and identifying exact wound margins can complicate measurement accuracy (Haghpanah et al. 2006; Keast et al. 2004). The use of low‐tech tools like paper rulers and depth probes often results in poor interobserver reliability and measurement inaccuracies (Haghpanah et al. 2006; Keast et al. 2004; Wang et al. 2017). Additionally, wound documentation is time‐consuming, particularly when photographing wounds. Digital cameras are employed for this purpose in clinical nursing practice at LMU University Hospital, and uploading these images to electronic patient records is often tedious and can be delayed by up to 2 days or more.

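### Shift workload is rated after the task, in the same questionnaire as task load, yet is adjusted for as a confounder, so the adjusted AI effect may be understated

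*Protocol article*

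**What the plan says.** **Timing and content.** Section 2.7 (Recruitment) places the survey after the documentation step. Once that step is finished, "the nurse will complete an online questionnaire on a tablet, which includes questions about demographic data, general workload of the shift, task load". The same instrument also asks about the usability of the system used. Task load is a dependent variable; shift workload is a predictor.

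**The measure.** Section 2.10 (Measures) describes "the general workload of the shift, which is assessed on a 5‐point scale relative to the average". It is the nurse's own judgement. Section 2.3 (Design) says neither participants nor observers can be blinded.

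**Its role.** Section 2.12 (Analysis Plan) will "incorporate potential covariates such as the nurses’ professional experience, wound severity, and the general load of the shift", with one linear model per dependent variable. The demonstrator's specific contribution is the difference in explained variance between the full model and a model without the demonstrator variable. Both models keep shift workload.

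**Missing values.** Under the same section, "datasets with missing values for independent variables will be excluded entirely". A missing dependent variable costs the case only the model concerned.

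**The concern.** A confounder should describe conditions that the exposure cannot have changed. Here the rating is given after the nurse has used one system or the other, in the same sitting as the rating of how demanding that work was. Section 2.1 (Objectives) expects the application to save time and lower task load. If it does, a nurse fresh from an easier episode may also call the shift lighter. The covariate would then carry part of the application's effect, and holding it constant would take that part away.

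The timing is the same in both phases, but this does not cancel the problem. What colours the rating is the task load just experienced, and that differs between phases by the effect under study.

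The full-versus-reduced comparison does not help either, because variance shared with the workload rating is already in the reduced model and is not credited to the demonstrator.

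A smaller matter follows from the missing-value rule. Shift workload comes only from the questionnaire. Any observed episode without one, for whatever reason, would leave every model, including the model for its care duration, which was timed directly.

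**Working it through.** The protocol gives no figure on this point. Its sample size is only background: with four predictors, alpha 0.05 and an assumed f² of 0.15 (the value is not printed), the overall F-test has power 0.803 at N = 85, and 85/0.9 = 94.4, so 95. Both stated numbers reproduce.

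**Set-up (all values below are assumptions).** Let A = 1 in the AI phase and 0 in the control phase, W0 the true shift load and Y the task load, with W0 and Y each having within-phase variance 1.
- Y = b·A + r·W0 + error, with b = -0.50 and r = 0.3 or 0.5.
- The late rating is W = W0 + k·Y, where k is the spill-over from task to rating.
- W0 is taken as equal in the two phases, so the adjusted effect would be b if k = 0.

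**Adjusted effect.**
- Within-phase covariance of W and Y: r + k.
- Within-phase variance of W: 1 + 2kr + k².
- Phase difference in W: k·b.
- Adjusted effect = b − k·b·(r + k)/(1 + 2kr + k²) = b·(1 + kr)/(1 + 2kr + k²).

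Example, k = 0.5 and r = 0.3: -0.50 × 1.15/1.55 = -0.371. With r = 0.5: -0.50 × 1.25/1.75 = -0.357.

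**R² difference.** With a 1:1 split, A has variance 1/4 and Y has total variance 1 + b²/4 = 1.0625. The increment is (adjusted effect)² × Var(A given W)/1.0625, where Var(A given W) = 1/4 − (k·b/4)²/(1 + 2kr + k² + k²b²/4). At k = 0 this is 0.25 × 0.25/1.0625 = 0.059. At k = 0.5, r = 0.3 it is 0.1376 × 0.2475/1.0625 = 0.032.

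| Spill-over k | Adjusted effect (r = 0.3 / 0.5) | Attenuation | R² difference (r = 0.3 / 0.5) |
|---|---|---|---|
| 0 | -0.50 / -0.50 | 0% | 0.059 / 0.059 |
| 0.2 | -0.46 / -0.44 | 9% / 11% | 0.049 / 0.046 |
| 0.3 | -0.43 / -0.41 | 14% / 17% | 0.043 / 0.040 |
| 0.5 | -0.37 / -0.36 | 26% / 29% | 0.032 / 0.030 |
| -0.2 | -0.51 / -0.54 | away from zero | 0.061 / 0.067 |

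Simulation agrees with the closed form. Entering the rating as a dummy-coded 5-point scale, as the plan intends, gives slightly less attenuation (about -0.37 to -0.39 at k = 0.5).

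**Against sampling error.** The standard error of the adjusted effect is roughly 2·√(1 − ρ²)/√85, with ρ² = (r + k)²/(1 + 2kr + k²). For k = 0.2, r = 0.3 this is 0.217 × √(1 − 0.216) = 0.19. For k = r = 0.5 it is 0.217 × √(1 − 0.571) = 0.14. The shift is 0.04 to 0.09 SD at k of 0.2 to 0.3, and 0.13 to 0.14 SD at k = 0.5.

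**The case against.** **The item concerns the whole shift, not the wound task.** This is fair. Nothing in the protocol shows that the rating is contaminated, and the direction is not certain: if a hard task makes the rest of the shift seem light by comparison, the bias runs away from zero. What stands is that the design cannot rule spill-over out and the planned analysis would not reveal it.

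**The shift is within noise for an exploratory pilot.** At moderate spill-over it is smaller than one standard error. It is systematic, however, and it falls on the quantity the plan uses to isolate the application's effect.

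**A sensitivity analysis may sit in a fuller plan that is not shown.** That is possible. The point rests on what the article does fix: the timing, the shared questionnaire, the covariate role and the model comparison.

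**Stronger readings a reader might infer.** None of these is supported.
- *Professional experience is affected in the same way.* It is a stable trait that a documentation system cannot change, and the article does not say when it is recorded.
- *Undocumented cases lose every outcome.* Section 2.7 gives the usual order of steps and does not say the questionnaire is withheld when documentation fails. The remark on "the likelihood that many wounds are not electronically documented" explains the daily telephone calls for case finding. The remark in the Background that "uploading these images to electronic patient records is often tedious and can be delayed by up to 2 days or more" describes routine image handling. Late documentation is provided for, since section 2.10 times it separately. An episode never documented would have no documentation duration in any event.
- *The item should simply be asked earlier.* Control collection closed in January 2024. Moving the item now would make its timing differ by phase, a measurement difference aligned with the exposure.

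**Conclusion.** The concern holds in a limited form. A subjective, unblinded rating taken after exposure and next to the task-load outcome is treated as a confounder in every model and in the full-versus-reduced comparison. Adjustment could therefore understate the application's effect on task load. Under the assumptions above the loss is about 9 to 17% at spill-over of 0.2 to 0.3 and 26 to 29% at 0.5; it is nil without spill-over. The spill-over, the true effect and the correlation are all assumed, and the protocol supplies none of them.

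The missing-data consequence is conditional and its size is unknown. The 10% allowance for dropout and missing data in section 2.6 protects the sample size, but it does not keep the two phases comparable if questionnaires are missing unequally.

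**What to change.** 1. Keep the timing of the workload item the same in both phases.
2. In the Analysis Plan, report the demonstrator effect (coefficient with confidence interval, and the R² difference) with and without the shift-workload term for each outcome, above all for task load. State in advance that an isolated demonstrator effect will not be claimed if the two versions disagree.
3. Report, by phase, how many observed episodes have no questionnaire, since the exclusion rule would remove their observed care duration from all models.

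The cost is one extra fit per outcome, a count, and a few sentences. There is a small downside: without the workload term, the model may carry more confounding from real differences in shift load between phases. It is a sensitivity analysis beside the planned model and does not replace it.
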